### Secondary outcomes

A number of secondary outcomes are defined in order to assess the safety, feasibility and potential additive benefits of both cellular therapy and associated immunosuppression minimisation on the clinical course of recipients post transplantation (figure 3). These secondary outcomes will be continuously monitored throughout the 18-month follow-up period post transplantation unless otherwise stated and can be further defined as follows:

#### Indicators of influence of Treg administration on graft outcome

**Figure 3 F3:**
[figure not shown]
Key time points alongside clinical and immune monitoring plans. EQ-5D-5L, EuroQol 5 Dimensions 5 Levels; HLA-DR, Human Leukocyte Antigen - DR Isotype; IMP, investigational medicinal product; QOL, Quality of Life; SF-36, 36 Item Short Form Survey; Treg, regulatory T cell.

Impact on acute rejection: Time to first acute rejection episode; severity of acute rejection episode based on response to treatment and histological scoring; total immunosuppressive burden at the final trial visit; and incidence of graft loss through rejection.

Success in reduction of immunosuppression: Proportion of patients on tacrolimus monotherapy at the end of the study.

Prevention of chronic graft dysfunction: Assessment of renal impairment, chronic allograft dysfunction and/or interstitial fibrosis and tubular atrophy assessed by clinical (impairment of estimated glomerular filtration rate (eGFR)) and histopathological (Banff staging) measures.

Avoidance of drug-related complications by immunosuppressant reduction: Incidence of drug-related adverse events.

### Patient survival

#### Markers of oversuppression of the immune system

Incidence of serious and/or opportunistic infections (especially CMV, Epstein Barr virus (EBV) and polyoma (BK) virus) and incidence of neoplasia.

#### Signs of chronic toxicity associated with infusion of cell products

Incidence of autoimmune disorders, anaemia, cytopenias or biochemical disturbances unrelated to the function of the transplanted kidney.

#### Patient quality of life

Patient quality of life will be measured in both arms of the study at pre-transplant baseline, 12 weeks, 51 weeks and 78 weeks post transplant using the 36 Item Short Form Survey (SF-36) and EuroQol 5 Dimensions 5 Levels (EQ-5D-5L) questionnaire.

### Immune monitoring

A critical component of the TWO study is comprehensive assessment of the impact of Treg infusion on the recipient’s immune repertoire and its capacity to respond to donor, third-party and non-allogeneic stimuli. Importantly, these assays will include analysis of whole blood and transplant biopsy samples taken from patients in both arms of the study. Assays remain experimental and will not be used to influence clinical decision-making in the TWO study. However, accumulating evidence suggests the potential for these tools in tailoring individualised immunosuppression regimens and we aim to identify those that might prove suitable for this purpose going forwards while providing important mechanistic information on a basic science level in the current study. Figure 3 provides an overview of immune monitoring assays being performed.

Absolute quantification of HLA-DR expression by peripheral blood monocytes is a useful and reproducible surrogate marker of innate immune responses. HLA-DR quantification will be performed by flow cytometry and interpreted using the following pre-determined ranges: Normal healthy controls >15 000 molecules per cell; immunodepression 15 000–8000 molecules per cell; immunoparesis <8000 molecules per cell.

Assays will be performed to investigate whether cell therapy shifts kidney transplant recipients towards a more tolerance-prone phenotype or away from a rejection-prone phenotype. Gene expression of a defined set of tolerance-associated genes in whole blood will be profiled by quantitative PCR. Leucocyte subset profiling will be performed by flow cytometry to quantify immune cell subpopulations in patient peripheral blood. Donor-reactive T cell frequencies will be measured following co-culture of recipient T cells with stored donor derived antigen presenting cells using a CD154/137 assay. This assay will be performed before and after transplantation to enable an estimation of the pre-transplant frequency of donor-reactive T cells, and detection of post-transplant sensitisation against donor antigen. Treg frequencies in patient blood will be measured by epigenetic analysis of the Treg-specific demethylated region of the FOXP3 gene. Finally, cytokine and metabolic profiling will be performed assessing inflammatory and regulatory cytokines as well as low-molecular-weight metabolites to provide a picture of the dynamic changes that may take place in the immune response after cellular therapy and immunosuppression modification.

Histopathological samples will be taken at 5 months (protocol biopsy) in kidney transplant recipients randomised to the TR001 arm. This biopsy will confirm the ongoing safety of Treg therapy and ensure no evidence of subclinical rejection. A 9-month protocol biopsy will be performed in all participants including the control arm to allow a histological comparison of the impact of Treg therapy.

### Sample size calculation

A standard anti-CD25 monoclonal antibody-based immunosuppression protocol as used in this study would be expected to result in a biopsy proven acute rejection rate of approximately 12%–20% over 18 months post transplant. Ekberg *et al* demonstrated that daclizumab induction with triple maintenance therapy of low-dose tacrolimus, myophenolate mofetil and corticosteroids resulted in acute rejection diagnoses in 12.3% of transplant recipients in the first year post transplant, a significant improvement on comparable alternative regimens at the time.^18^ Recently, the 3C study reported a 16% acute rejection rate in the first 6 months of a basiliximab-based immunosuppression regimen and a further 3% over the following 18 months up to 2 years post transplant.^19 20^ There is little data on anticipated rejection rates in patients treated with Treg therapy. We reported in our phase 1 trial a rejection rate of 21.1% in a control cohort receiving basiliximab-based immunosuppression compared with no rejection episodes in patients receiving Treg therapy over 60 weeks post transplant.^13^ In contrast, Roemchild *et al*, demonstrated a rejection rate of 27% in patients treated with polyclonal Treg therapy and 22% in an identical control cohort.^15^ However, numbers were small in both studies and although both used autologous polyclonal Treg the manufacturing processes and quality control assessment of the final product differed.

The TWO study is a phase 2b study aimed at proving the feasibility, ongoing safety and exploring the efficacy of Treg therapy to facilitate a reduction in standard immunosuppression. We aim to provide the data required for future phase 3 sample size calculations. Recruitment of 30 participants in each arm will allow us to estimate rejection rates in both arms with an anticipated 80% Wilson CI width between 10% and 23%, depending on the observed rate.

### Data analysis plan

This early phase study will report data using 20% statistical significance and 80% CIs.

Two analysis sets will be defined:

Intention-to-treat population: all patients who signed informed consent and were transplanted will be analysed in the groups to which they were randomised.Per-protocol population: all patients who signed informed consent, were transplanted and were treated according to protocol specifications.

Descriptive statistics will be used to describe the demographics between the treatment groups. Withdrawn patients will also be described fully. Comparative analysis will be undertaken to provide an indication as to whether a definitive phase 3 randomised trial would be appropriate.

For continuous variables, the difference in the means and the corresponding 80% CI will be reported for each treatment group and overall. For continuous variables, t-tests unadjusted or multivariable linear models adjusted for important factors will be applied.

For categorical variables, the number (and percentage) of patients in each category will be reported for each treatment group and overall. For categorical variables, χ^2^ tests will be used for comparing treatment groups or multivariable logistic models adjusted for important factors.

The primary outcome is biopsy proven acute rejection episode and the time to first biopsy proven acute rejection will be analysed using survival analysis techniques. Kaplan-Meier survival curves will be presented graphically. Cox proportional hazards models will be used both unadjusted and adjusted for important factors. The log-rank test will be used to identify significance. Acute rejection rates at 18 months will be reported for both groups and as a difference in proportions, alongside the HRs and 80% CI will be reported. Patients who have been withdrawn or lost to follow-up will be censored at their last known rejection-free time. Analysis adjusting for competing risks of allograft failure or death will be considered.

No interim analyses are planned, but a data safety and monitoring committee (DSMC) will review descriptive summaries of accumulating data and make recommendations on trial termination or modification to the TSC based on these data. The independent members of the DSMC panel are chosen from those leading in the field of clinical transplantation and/or with experience of previous cell therapy trials in the ONE study consortium. They will conduct a review of data at least annually at the discretion of the committee and will be informed of any serious adverse reactions (SARs) or suspected unexpected serious adverse reactions (SUSARs) as they occur by email notification. The DSMC charter is available from the TWO study team.

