**Methods and analysis:**

60 patients will be randomised on a 1:1 basis to Treg therapy (TR001) or standard clinical care (control). Patients in the TR001 arm will receive an infusion of autologous polyclonal ex vivo expanded Tregs 5 days after transplantation instead of standard monoclonal antibody induction. Maintenance immunosuppression will be reduced over the course of the post-transplant period to low-dose tacrolimus monotherapy. Control participants will receive a standard basiliximab-based immunosuppression regimen with long-term tacrolimus and mycophenolate mofetil immunosuppression. The primary endpoint is biopsy proven acute rejection over 18 months; secondary endpoints include immunosuppression burden, chronic graft dysfunction and drug-related complications.

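### For continuous outcomes the plan ranks an unadjusted t-test equally with an adjusted model, although SF-36 and EQ-5D-5L have a pre-transplant baseline that could sharpen the comparison

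*Protocol article*

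**What the plan says.** Under Patient quality of life, the protocol article schedules two questionnaires, SF-36 and EQ-5D-5L, in both arms: "at pre-transplant baseline, 12 weeks, 51 weeks and 78 weeks post transplant". Each patient should therefore have one score before transplant and three after it.

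Under Data analysis plan, one sentence governs every continuous variable: "For continuous variables, t-tests unadjusted or multivariable linear models adjusted for important factors will be applied". No order of preference is given, the factors are not listed, and the baseline value of the outcome is not mentioned. The section also sets the reporting standard: "This early phase study will report data using 20% statistical significance and 80% CIs". For the primary outcome, by contrast, it commits to reporting Cox models both with and without adjustment.

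Under Study design, allocation is by minimisation on ethnicity and HLA-DR mismatch. Quality of life is not a minimisation factor.

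**The concern.** When an outcome is measured before and after treatment, a comparison of follow-up scores alone leaves in the error term whatever variation the baseline could explain. With 30 patients per arm that may matter, and the remedy uses data the trial already plans to collect. The article does not simply leave the model to a later document: it names the unadjusted test as one of two acceptable analyses, on an equal footing with the adjusted one.

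At stake is the width of the interval around the quality-of-life difference. The secondary outcomes are there partly to show whether cell therapy with reduced immunosuppression brings added benefit, and the comparative analyses are meant to indicate whether a phase 3 trial is appropriate. An interval wider than it need be makes that reading harder.

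**Working it through.** **The plan's own precision figure.** The only one given concerns the rejection rate in each arm of 30, for which the Sample size calculation promises an estimate "with an anticipated 80% Wilson CI width between 10% and 23%, depending on the observed rate". The Wilson width is 2z√(p(1−p)/n + z²/4n²) / (1 + z²/n), with n = 30 and z = 1.2816.

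- 1 event in 30: 9.5%
- 15 events in 30: 22.8%

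The stated 10% to 23% is therefore reproduced (only 0 in 30 falls below it, at 5.2%). No precision is stated for quality of life or any other continuous outcome.

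**Inputs**

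- 30 per arm, 1:1 (Sample size calculation; Study design).
- 80% CI (Data analysis plan), so the 0.90 quantile of t is used.
- Correlation ρ between baseline and follow-up score: not in the documents. It is an assumption, shown over a range.
- Complete data, and baseline score as the only covariate: simplifying assumptions.

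**Formulas**, as 80% CI half-widths in units of the outcome SD:

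- Unadjusted t-test on the follow-up score: t(0.90, 58) × √(2/30) = 1.2963 × 0.2582 = 0.335.
- Adjusted for baseline (ANCOVA): t(0.90, 57) × √(2/30) × √(1−ρ²) × √(1 + 1/56) = 1.2966 × 0.2582 × 1.0089 × √(1−ρ²) = 0.338 × √(1−ρ²). The factor √(1 + 1/56) is the small-sample cost of estimating the baseline slope.
- Unadjusted t-test on change from baseline: 0.335 × √(2(1−ρ)).

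**Results**

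| Assumed ρ | t-test, follow-up | ANCOVA | ANCOVA width relative to t-test | t-test, change | 30/(1−ρ²) |
|---|---|---|---|---|---|
| 0 | 0.335 | 0.338 | 1% wider | 0.473 | 30.0 |
| 0.2 | 0.335 | 0.331 | 1% narrower | 0.423 | 31.2 |
| 0.3 | 0.335 | 0.322 | 4% narrower | 0.396 | 33.0 |
| 0.5 | 0.335 | 0.293 | 13% narrower | 0.335 | 40.0 |
| 0.7 | 0.335 | 0.241 | 28% narrower | 0.259 | 58.8 |

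The last column is the number per arm that an unadjusted analysis would need for the same variance. It leaves out the small-sample factor, so it slightly flatters the adjusted analysis. A t-test on change uses the baseline, but does worse than ignoring it when ρ is below 0.5, and it is wider than ANCOVA at every ρ in the table.

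**The case against.** The strongest reply is that the choice of model, covariates and time point for a secondary questionnaire belongs in the statistical analysis plan, which is not shown, and that a journal article condenses a longer protocol. This stands to the extent that the full documents may already settle the matter, in which case the sponsor need only say so. It does not remove the point, because the article states an analysis, and one of the two it states is the less efficient method.

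Three further objections stand and limit the claim.

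- A reader might infer that the plan throws the baseline away. It does not say that. The adjusted alternative could include the baseline score among its factors, and a t-test on change scores would also use it.
- A reader might infer that chance imbalance at baseline makes the unadjusted result wrong. It does not. The randomised comparison is unbiased, its interval already allows for chance imbalance, and any imbalance carries over to follow-up only in proportion to ρ. The issue is efficiency, not validity.
- A reader might take a gain equivalent to 10 or more extra patients per arm as established. That requires ρ of at least 0.5. The baseline here precedes a kidney transplant and the last score comes 78 weeks after it, so a low correlation cannot be excluded. At 0.2 the gain is about 1%.

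Nor do the documents support a reading that the method would be picked after seeing both results. The wording leaves the order open and says nothing about how it would be resolved.

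Last, adjustment is not wholly free of conditions. Venesection for manufacture takes place at least 3 weeks before transplant in the cell therapy arm, so allocation is known well before surgery in an open-label trial. The article describes the questionnaire only as pre-transplant and does not say whether it precedes randomisation.

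**Conclusion.** The point holds as a limited one. The plan permits, without ranking it, an unadjusted t-test for outcomes that have a baseline in both arms, and leaves the covariates of the alternative model unnamed. The t-test is valid, but it gives up precision if baseline and follow-up scores are at least moderately correlated: the 80% CI half-width is 0.335 SD, against 0.322 to 0.241 SD with adjustment for ρ of 0.3 to 0.7. At ρ of about 0.2 or less the difference is negligible, and at zero the adjusted interval is about 1% wider. These figures rest on an assumed ρ, complete data and a single covariate.

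The matter concerns an exploratory secondary outcome in a trial that the article itself describes as not powered for definitive efficacy. The analysis of biopsy-proven rejection and the 10% to 23% Wilson widths are unaffected.

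**What to change.** For SF-36 and EQ-5D-5L, state one main analysis: a linear model with arm, baseline score, ethnicity and HLA-DR mismatch, either as ANCOVA at week 78 or as a mixed model across the post-transplant visits. Report the adjusted difference between arms with its 80% CI. Keep any unadjusted t-test as supportive only. If the statistical analysis plan already says this, confirm it and bring the general sentence into line.

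The cost is a change of wording, since the baseline is already scheduled, plus a few degrees of freedom. Baseline adjustment alone widens the interval by about 1% if the correlation is near zero; the two minimisation factors use a little more, depending on how many levels they have. Before fixing the model, confirm that the baseline questionnaire is completed before randomisation, or at least before transplant. If it is completed after allocation is known, say so when the adjusted result is reported.

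### Banff stage is an ordered outcome, but the only unadjusted test the plan gives categorical variables is a chi-square test, which ignores the order

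*Protocol article*

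**What the plan says.** Under Secondary outcomes, chronic graft dysfunction (including interstitial fibrosis and tubular atrophy) is assessed clinically through eGFR and by "histopathological (Banff staging) measures". Under Immune monitoring, the 5-month protocol biopsy is for the TR001 arm only, whereas "A 9-month protocol biopsy will be performed in all participants including the control arm", and the reason given is "to allow a histological comparison of the impact of Treg therapy".

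The Data analysis plan sets the level: "This early phase study will report data using 20% statistical significance and 80% CIs". Apart from the survival analysis of rejection, it has two rules. Continuous variables get t-tests or linear models. For categorical variables, "the number (and percentage) of patients in each category will be reported for each treatment group and overall", and chi-square "tests will be used for comparing treatment groups or multivariable logistic models adjusted for important factors". The type of logistic model is not stated, and no method for ordered categories is named. Banff stage is not assigned to a test by name.

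**The concern.** A Banff stage runs from less to more damage, and the question put to it has a direction: is there more or less chronic damage after Treg therapy with reduced immunosuppression? A chi-square test on the full table gives the same p-value however the grades are shuffled. It spreads its sensitivity over every possible pattern of difference (3 degrees of freedom with four grades, 2 with three), and it gives no effect estimate with a sign.

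The 9-month biopsy is the only scheduled histology taken in both arms. The comparative analyses are meant to indicate whether a phase 3 trial is worthwhile. With 60 patients, a modest but consistent shift across grades could go unflagged by chi-square when an ordered test on the same data would flag it.

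**Working it through.** **Inputs from the documents.** "Recruitment of 30 participants in each arm" (Sample size calculation); "60 patients will be randomised on a 1:1 basis" (Abstract); 20% significance with 80% CIs (Data analysis plan). Sidedness is not stated; two-sided is assumed because it matches the 80% CIs.

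**Inputs not in the documents, hence assumed.** Number of grades (four or three); control distribution (six four-grade distributions from 70/20/7/3% to 25/25/25/25%, and two three-grade ones); effect (a proportional-odds shift with odds ratio 1.5 to 4).

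**Step 1. The plan's own design figure.** The only one is the 80% Wilson interval width for a rejection rate, 10% to 23%. With n = 30 and z = 1.2816:

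width = [2z / (1 + z²/n)] × √[p(1−p)/n + z²/(4n²)]

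The first factor is 2 × 1.2816 / (1 + 1.6425/30) = 2.430.
- 15 events (p = 0.5): 2.430 × √(0.008333 + 0.000456) = 22.8%.
- 1 event (p = 1/30): 2.430 × √(0.001074 + 0.000456) = 9.5%.

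This reproduces the stated range, given at least one event (with none the width is 5.2%). It concerns rejection only. No power or precision is stated for histology.

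**Step 2. What a proportional-odds shift looks like.** Take control grades 50/30/15/5% and an odds ratio of 2.5 towards less damage.
- Cumulative proportions 50, 80, 95% have odds 1, 4, 19.
- Multiplied by 2.5 these become 2.5, 10, 47.5, or cumulative 71.4, 90.9, 97.9%.
- The treated grades are therefore 71.4/19.5/7.0/2.1%.

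**Step 3. Compare the tests by simulation.** Grades are drawn for 30 patients per arm and tested at the two-sided 20% level with the Pearson chi-square on the full table and with the tie-corrected Wilcoxon rank-sum test. The latter is the score test of the unadjusted proportional-odds model. In the Step 2 example, power is 56.0% for chi-square and 68.9% for the ordered test, a difference of 12.9 points.

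Gain of the ordered test over chi-square, in percentage points:

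| Odds ratio | Four grades | Three grades |
|---|---|---|
| 1.5 | 4.5–5.9 | 1.5–3.0 |
| 2 | 8.9–11.4 | 5.3–6.9 (over 2 to 3) |
| 2.5 | 11.8–12.9 | as above |
| 3 | 11.3–12.7 | as above |
| 4 | 7.2–12.2 | 3.6–5.3 |

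With 25 evaluable biopsies per arm, the four-grade gain at odds ratios 2 to 3 is 8.1–12.9. With no true difference, both tests reject about 20–21% of the time for control distributions from 30/40/20/10% to 60/25/10/5%. The gain is therefore not bought with false positives.

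**Step 4. Compare with a yes/no cut.** If the logistic route means a binary model, the result depends on the cut. With four grades and odds ratios 2 to 3, the ordered test gains −2.9 to +6.9 points over any-versus-none, and +2.2 to +23.3 points over a cut at grade 2 or above. The near-parity of any-versus-none is partly an artefact: at 30 per arm its actual rejection rate under no difference reaches about 25%, because the counts are so discrete.

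**The case against.** The strongest reply is that this is detail for the statistical analysis plan, which is not shown. The article condenses a longer protocol, gives one generic sentence per variable type, never ties Banff stage to a test, and does not say whether histology will be analysed as a full grade, a score or present/absent. The sentence on the 9-month biopsy does not name fibrosis stage, so linking it to the chronic graft dysfunction outcome is an inference, though a natural one. The outcome is secondary, the article itself says the trial is not powered for definitive efficacy, and grade counts by arm will be shown anyway, so a clear shift would be visible.

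Much of this stands as a limit on importance. It does not remove the point, because the section is not silent: it states a rule for all categorical variables, and the only unadjusted test in that rule ignores order.

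Three stronger readings are tempting and not supported:
- A reader might infer that the plan commits to a binary logistic model. The text says only that the models are logistic and multivariable, which does not exclude an ordinal one.
- A reader might take a loss of 10 to 13 points as the general cost. That holds only for chi-square, with four grades and an odds ratio of about 2 to 3. It does not carry over to a logistic model, and every simulated alternative is a proportional-odds shift, which favours the ordered test.
- A reader might infer that no directional estimate could result. Any logistic model gives an odds ratio, and the section promises 80% CIs in general. Only the chi-square route lacks one.

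**Conclusion.** The point holds as a modest one. The stated categorical rule gives an ordered Banff stage an unordered unadjusted test and leaves the type of adjusted model open. With 30 per arm at the two-sided 20% level, and proportional-odds shifts of 1.5 to 4, the cost against chi-square is about 5 to 13 points of power with four grades and about 1.5 to 7 with three. Against a binary cut it ranges from none to over 20 points. These ranges rest wholly on assumed grade distributions and effects.

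Only the histological part of one exploratory secondary outcome is affected. eGFR falls under the continuous rule, and the rejection analysis is separate.

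**What to change.** Add one sentence to the Data analysis plan: ordered outcomes such as Banff stage will be compared with a Wilcoxon rank-sum or linear trend test (unadjusted) and a proportional-odds logistic model (adjusted), reporting the common odds ratio with its 80% CI. Keep the number and percentage in each grade by arm. Reserve chi-square and binary logistic models for unordered or truly binary outcomes.

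This needs no extra patients, biopsies or data. The small downside is that the common odds ratio assumes a broadly consistent shift across grades. The Wilcoxon test remains valid as a test without that assumption, and the grade table lets readers judge whether the shift is consistent.
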